### Outcome determination

Primary outcome determination will be through data obtained from the provincial government health administrative databases and from the CSQ to determine the expulsion rate for each group at 1 year. Permission will be obtained from participants to use personal health numbers (the unique identifiers used in these databases) and date of birth to search these databases, detailing all subsequent care received in BC within the subsequent year (including IUD removals and re-insertions, and prescriptions for alternate forms of birth control; information on subsequent pregnancies such as miscarriages, abortions, or deliveries; and any hospital re-admissions, surgery or prescriptions dispensed for antibiotics, which may indicate possible complications). The CSQ will collect data on expulsion of IUD, effectiveness of and satisfaction with the contraceptive method and insertion timing assigned, any removal of the IUD, any change to contraceptive method or intention to conceive, any interval pregnancies and their outcomes, and any adverse events. Using both the databases and the CSQ methods for outcome determination over a period of 5 years (the device life for the IUDs) we will determine, with a close to perfect follow-up rate, the intention to treat (ITT) effectiveness of post-abortion contraception in Canada.

### Ethical considerations

This study has received institutional review board approval from the University of British Columbia-Children’s and Women’s Research Ethics Board (H10-00798) and the Interior Health Authority Research Ethics Board (2010-034).

#### Analysis

Primary outcome will be examined as expulsion rate at 1 year for women randomized to receive the FlexiT device compared with women randomized to a NovaT. Secondary outcomes will be examined annually over the 5-year period using an ITT framework for both randomized and non-intervention groups, and will include: pregnancy rate, rate for continuation of method, adverse events (such as infection or perforation), outcomes of those participants who were chlamydia-positive at the time of abortion, and satisfaction with contraceptive method chosen and expulsion rate for years 2 to 5.

### Analysis methods

Because our aim is to examine expulsion rates and establish the non-inferiority (within a margin of 10%) of the Flexi-T compared with the NovaT, the primary analysis will be based on an upper (one-sided) 95% confidence limit for the difference in expulsion rates (FlexiT rate minus NovaT rate). Non-inferiority will be inferred if the confidence limit value is less than 10%. This simple approach is valid so long as no systematic difference in follow-up occurs between groups. As a check, we will also conduct analysis to account for partial follow-up. Because our outcome definition is essentially composite and the relevant risk periods differ by components, Kaplan-Meier estimates for each component event will be determined, and composite estimates will be obtained by summing the estimated cumulative event rates (calculated as 1 minus the survival function) at the time points indicated in our operational definitions. Confidence intervals around the difference in these estimates will be calculated using the bootstrap method.

Rates for all secondary outcomes will be calculated in an ITT framework for events occurring within 1year and within successive years following the abortion, and for pregnancy events, those associated with a conception within a year or successive years. Outcomes will be determined using the CSQ, direct access to clinical follow-up visit records, and billing and procedure coding data from the administrative health-system databases. Multivariate logistic regression will be used to examine demographic, socioeconomic, and obstetric factors in relationship to primary and secondary objectives.

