### Sample-size justification for comparing expulsion rates for the NovaT and FlexiT

Our aim in this non-inferiority study is to provide evidence that the expulsion rate for the Flexi-T does not exceed that of the Nova-T by more than 10%. The rationale for this choice rests on the assumption that the detection rate for IUD expulsions is at least 85% 
[20], which implies that the loss in efficacy of a device due to expulsions is less than 0.15 times its expulsion rate, and correspondingly, that any difference in efficacy between devices is less than 0.15 times the difference in expulsion rates. Thus differences of 10% in expulsion rates translate into differences in efficacy of 1.5% or less.

We calculated power calculations for non-inferiority testing following the approach described by Blackwelder 
[21] using the on-line calculator provided by S. Patten 
[22].

Our null hypothesis is: H_0_: FlexiT expulsion rate ≥ NovaT expulsion rate + 10%.

This formula requires specification of the problem in terms of success proportions (that is, those not experiencing expulsion by 1 year). We will assume the rate of those not experiencing expulsion will be 96% for the Nova-T 
[17-19] and 92% for the Flexi-T. Thus, we require a sample size of 192 per group to attain 80% power at α = 0.05 to detect a difference in expulsion rates exceeding 10%. We will enroll a total of 400 women, a sufficient number to allow for changes to intention to leave the province and thus loss to follow-up using the health administrative databases. This recruitment will ensure the final sample is at least the 384 women required to test the null hypothesis that FlexiT has a significantly inferior (higher) expulsion rate compared with the NovaT.

Thus, our recruitment will include 400 women who choose to have IUDs and consent to be randomized to either the Flexi-T (200 women) or the Nova-T (200 women), and a further 200 who decide to not to use intrauterine contraception, who will be enrolled as a non-intervention comparator group. Therefore, a total of 600 women will be recruited.

The study clinic (see ‘Recruitment facility’, below) provides abortions to about 700 women meeting the entry criteria each year, and based on our previous research in this setting 
[23] we expect 40% of eligible women to choose an IUD, and 80% of these to enroll in IUD groups. Target enrollment is anticipated at 22 months.

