### Enrollment process

All women presenting at the study clinic for an abortion of a pregnancy before 12 weeks gestational age will receive information via the research study web page 
[24] at the time they book their appointment, and a study information brochure upon check-in. All women will undergo a post-abortion contraception information session with a trained clinic nurse who is not part of the research staff, and the women will decide upon their contraceptive method of choice before they are asked if they wish to participate in the study. Interested potential participants will then be referred for an information session with a trained women’s health research assistant (RA). The RA will explain all study procedures, answer all questions, and complete the informed consent process with women before the time of their abortion, including establishing preferred personal contact methods to ensure follow-up. Enrolled women will complete an intake version of the contraception satisfaction questionnaire (CSQ) on site. We have previously described the development and use of the CSQ 
[23]. Briefly, this is a detailed instrument eliciting the effectiveness of, degree of satisfaction with, and adverse effects experienced for the range of contraceptive methods available in Canada. The CSQ has been adapted from a published instrument 
[25,26] for use in post-abortion studies. It has been translated into the three most common non-English languages in our study population, and piloted for accuracy and cultural sensitivity. This trial has been registered at ClinicalTrials.Gov (Identifier: NCT01174225).

Participants choosing a copper IUD will be randomized to receive either the Flexi-T or the Nova-T. Stratified (that is, separate) randomization lists in sequential blocks of sizes of eight will be generated for parous and nulliparous women. Allocation will be performed remotely using a Canadian on-line randomization service (http://www.randomize.net 

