#### Expulsions

Most women will be aware when an IUD expulsion occurs 
[20], and should it occur, will make arrangements for alternative contraception. This alternative contraception may be a replacement device or a change in contraceptive method. Each participant will be provided with a toll-free number enabling them to contact the principal investigator ([name]) at any time. In addition, the study team will monitor follow-up visits, CSQs, government medical plan billings, and prescription records of alternative contraception prescribed or an IUD removed or inserted. In this manner, we believe we will be able to estimate device expulsion rate with a fair degree of accuracy. To reflect usual contraceptive conditions most accurately in the event of an expulsion, we are not providing a free replacement device. We have stratified at randomization for parity, as this may be a confounding factor in expulsion.

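### Randomisation is stratified by parity but the primary non-inferiority limit ignores parity: a small mismatch, mended by a parity-stratified score-type limit

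*Protocol article*

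**What the plan says.** All references are to the protocol article.

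- **Enrollment process:** "Stratified (that is, separate) randomization lists in sequential blocks of sizes of eight will be generated for parous and nulliparous women".
- **Anticipated limitations, Expulsions:** the reason given is "We have stratified at randomization for parity, as this may be a confounding factor in expulsion". Expulsion at 1 year is the primary outcome.
- **Analysis methods:** "the primary analysis will be based on an upper (one-sided) 95% confidence limit for the difference in expulsion rates (FlexiT rate minus NovaT rate". Non-inferiority is inferred if that limit is below 10%. The only condition set on the method is that "This simple approach is valid so long as no systematic difference in follow-up occurs between groups". A Kaplan-Meier and bootstrap check is added for partial follow-up, also without parity. A logistic regression will examine obstetric and other factors, but it is not tied to the non-inferiority limit.
- **Sample-size justification:** "We calculated power calculations for non-inferiority testing following the approach described by Blackwelder"; the assumption that "the rate of those not experiencing expulsion will be 96% for the Nova-T" (92% for FlexiT); and "we require a sample size of 192 per group to attain 80% power at α = 0.05". Planned enrolment is 200 per group. Parity plays no part in the calculation.

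**The concern.** The design treats parity as possibly prognostic for the primary outcome, and the primary limit then ignores it. Two things follow.

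First, a standard error from two simple proportions includes the between-parity variation that stratified allocation has balanced out. If parity matters, the limit is slightly wider than the design warrants.

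Second, blocking balances parity only at allocation. The Exclusion criteria then remove some randomised women (perforation or excessive bleeding at the abortion, no procedure, uterine anomaly), and the Sample-size justification allows for women leaving the province. A simple difference carries any parity imbalance that results; a stratified one largely removes it.

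What is at stake is the exact position of one upper limit against a 10-point margin. It would matter only for a result close to that margin.

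**Working it through.** **1. The plan's own figure.** Expulsion is 4% (NovaT) and 8% (FlexiT), the margin is 10 points and one-sided alpha is 0.05. The distance from the expected difference to the margin is 0.10 − 0.04 = 0.06.

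- Variance term: V = 0.04×0.96 + 0.08×0.92 = 0.112.
- n = V(1.645 + 0.842)²/0.06² = 192.35 per group, against 192 stated. It reproduces.
- Power = Φ(0.06/√(V/n) − 1.645): 79.9% at 192 and 81.3% at 200.
- Expected expulsions at 200 per group: 8 + 16 = 24.

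**2. Stratified variance.** The article gives neither the parity mix nor the parity effect, so both are assumed. Example with risk ratio 4 and equal strata: NovaT 1.6% and 6.4%, FlexiT 3.2% and 12.8%.

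- V = 0.5(0.016×0.984 + 0.064×0.936) + 0.5(0.032×0.968 + 0.128×0.872) = 0.1091, or 97.4% of 0.112.
- Power at 200 = Φ(0.06/√(0.1091/200) − 1.645) = 82.2%.

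| Assumed parity risk ratio | Power at 200, 30–70% of women in the higher-risk stratum | Equal strata |
|---|---|---|
| 1 | 81.3% | 81.3% |
| 2 | 81.5–81.7% | 81.6% |
| 3 | 81.7–82.1% | 82.0% |
| 4 | 81.8–82.6% | 82.2% |

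The distance from estimate to limit goes from 3.89 points to 3.84 at risk ratio 4 with equal strata.

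**3. Is true precision lost?** Trials of 400 women in stratified blocks of eight were simulated (200,000 per setting). At risk ratio 3 with 40% in the higher-risk stratum, the actual standard deviation was 0.0234 for both the crude and the stratified difference. Only the estimated standard error shrinks.

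**4. Error rate at the margin (4% against 14%).** Across risk ratios 1 to 5 and mixes of 40% or 60%, simple Wald limits gave 5.10–5.72% crude and 5.75–5.89% stratified. The cells are sparse. In the example of step 2, the lower-risk NovaT cell has about 100 women at 1.6%, so the chance of no event is 0.984^100 = 20%. A bootstrap within that cell would then give it zero variance.

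**5. Score-type limit.** In a further simulation (risk ratio 1 to 4; 30%, 50% or 70% in the higher-risk stratum; at least 60,000 trials per setting), the stratified Miettinen-Nurminen limit had an error rate of about 4% to 5%. Power was about 76–77%, no better than a crude score limit and up to about 1 point lower at risk ratio 4.

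A hand check of the crude score limit agrees. Constraining the difference to 10 points, the restricted rates are about 2.82% and 12.82%. The null variance term is 0.0282×0.9718 + 0.1282×0.8718 = 0.139. Power at 200 = Φ((0.06 − 1.645√(0.139/200))/√(0.112/200)) ≈ Φ(0.70) ≈ 76%. The gap from 81.3% comes from the type of interval, not from stratifying.

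**6. Imbalance after randomisation.** Assume 6% average expulsion, equal strata overall and a 5-point difference in parity mix between arms. The crude estimate shifts by 0.05×(0.08 − 0.04) = 0.2 points at risk ratio 2, and by 0.05×(0.09 − 0.03) = 0.3 points at risk ratio 3. The article gives no expected imbalance.

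**The case against.** The case against is substantial.

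- **No error is shown.** The simple difference is unbiased under this randomisation, and its limit is if anything mildly conservative relative to a stratified one. This stands.
- **The blocks have already done the work.** They secure the true precision and prevent chance imbalance at allocation. This stands. A reader might infer that the plan throws away free precision or is exposed to chance imbalance; the stratified lists rule out most of both.
- **The premise is tentative.** The article says only that parity may matter, and gives no mix or effect. This stands; every gain above is conditional on assumed values.
- **Imbalance after randomisation should be slight.** The listed exclusions arise from the abortion rather than the device, near-complete follow-up is expected, and only 16 losses in 400 are allowed for. This stands as to size, but does not remove the possibility.
- **The estimator may be set in an analysis plan that is not shown.** The article never calls the difference unadjusted, and a stratified risk difference is also a difference in rates. This stands in part. The article does, however, call its method simple and states a validity condition that mentions only follow-up, so as written the stratification factor is left out.
- **Adjustment is not free.** A stratified Wald limit raises the error rate. This stands, and it decides the form of the fix.

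**Conclusion.** The mismatch between stratified randomisation and an unstratified primary limit is real and minor. It is worth about 1 power point for an assumed parity risk ratio up to 4 (0.5 to 1.3 points across the assumed mixes at 4), and nothing if parity has no effect. Even that gain appears only with the Wald-type variance, whose error rate runs above 5%; with a score-type limit it disappears. What remains is consistency with the randomisation, protection against parity imbalance after exclusions or losses, and an estimator fixed before outcomes are seen.

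A reader might conclude that the non-inferiority comparison is biased or invalid, or that the trial is too small because parity is ignored. The article supports neither: the comparison is valid by design, and 192 per group reproduces from its stated inputs. These conclusions rest on the article's 4% and 8% expulsion rates and on assumed parity mixes and risk ratios.

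**What to change.** In Analysis methods, state that the primary one-sided 95% upper limit will be computed for the parity-stratified risk difference (FlexiT minus NovaT) with a score-type method, for example stratified Miettinen-Nurminen, and that the crude difference will be shown as supportive. Do not use a stratified Wald limit or a bootstrap within arm-by-parity cells for this purpose. If the simple difference is kept instead, say that this is deliberate.

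Cost: one sentence and slightly more analysis work. Parity is already recorded for randomisation, so no new data are needed, and stratifying by itself calls for no change in sample size. The team should know before choosing that a score-type limit, stratified or not, has about 76–77% power at 200 per group on the plan's own rates, against the 81.3% that the planning formula gives. That is the price of keeping the error rate within 5%.

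### Equal follow-up in the two arms is not enough to make the crude expulsion difference valid against a 10-point non-inferiority margin

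*Protocol article*

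**What the plan says.** Under Analysis methods, "the primary analysis will be based on an upper (one-sided) 95% confidence limit for the difference in expulsion rates", taken as FlexiT minus NovaT. The decision rule is: "Non-inferiority will be inferred if the confidence limit value is less than 10" percent. The protocol then says of this crude comparison: "This simple approach is valid so long as no systematic difference in follow-up occurs between groups". It continues: "As a check, we will also conduct analysis to account for partial follow-up". That second analysis sums Kaplan-Meier estimates of the component events and puts a bootstrap interval around the difference.

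Outcome determination takes the primary outcome from provincial administrative databases and the satisfaction questionnaire, and expects almost complete follow-up. The limitations section on Expulsions adds follow-up visits and a telephone line, and concludes: "we believe we will be able to estimate device expulsion rate with a fair degree of accuracy". The sample-size section enrols 400 women so that at least 384 remain after some leave the province. The article does not say whether a woman with incomplete follow-up and no recorded expulsion counts as not expelled or leaves the denominator.

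**The concern.** Balanced losses are a familiar safeguard when the null hypothesis is no difference: equal under-recording of equal rates still leaves a difference of zero. Here the null boundary is a difference of 10 points. If the same share of expulsions goes unrecorded in both arms, both rates are multiplied by the same factor, and so is their difference. A FlexiT device that sits exactly on the margin then appears to be inside it.

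Such under-recording is plausible. The database items listed under Outcome determination (removals, re-insertions, prescriptions, pregnancies, hospital care) are traces of care that a woman sought. She can be fully linked in billing data while an expulsion leaves no record. At stake is the one-sided 5% error of the primary claim: the stated condition can be met while the error rate is above its nominal level, in the direction that favours success.

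**Working it through.** **Inputs.** From the sample-size section: "We will assume the rate of those not experiencing expulsion will be 96% for the Nova-T" (4% expelled), 92% for FlexiT (8% expelled), a margin of 10 points, and 200 women per arm enrolled. The null is "FlexiT expulsion rate ≥ NovaT expulsion rate + 10" points, so its boundary at the assumed NovaT rate is 14% v 4%. The loss allowance is (400 − 384)/400 = 4%. The one-sided 95% limit comes from Analysis methods. Assumption: an unpooled Wald limit, because the article names no interval method.

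**1. The plan's own figure.** The protocol states: "we require a sample size of 192 per group to attain 80% power at α = 0.05". The Blackwelder formula gives n = (1.645 + 0.842)² × (0.96 × 0.04 + 0.92 × 0.08) / (0.10 − 0.04)² = 6.183 × 0.112 / 0.0036 = 192.3. The stated 192 is reproduced with one-sided α = 0.05. One-sided 0.025 would need 245.

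**2. Case A: incompletely followed women count as not expelled.** Let m be the share of expulsions unseen, equal in both arms. The observed rates are 0.14(1 − m) and 0.04(1 − m), and the observed difference is 0.10(1 − m). The false-claim rate is approximately Φ[(0.10 − difference)/SE − 1.645], with SE = √{[pF(1 − pF) + pN(1 − pN)]/200}. For m = 4% the rates are 13.44% and 3.84%, SE = 0.02768, and the result is Φ(0.004/0.02768 − 1.645) = Φ(−1.500) = 6.7%. The exact figures sum the binomial probabilities of all outcomes that meet the decision rule.

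| Unseen in each arm | Observed difference (points) | Normal approximation | Exact |
|---|---|---|---|
| 0% | 10.0 | 5.0% | 5.6% |
| 4% (loss allowance) | 9.6 | 6.7% | 7.4% |
| 10% (assumed) | 9.0 | 10.1% | 11.2% |
| 15% (assumed) | 8.5 | 14.2% | 15.4% |
| 20% (assumed) | 8.0 | 19.4% | 21.0% |

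The exact 5.6% in the first row is a property of the Wald limit, not of follow-up.

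**3. Case B: lost women excluded, equal loss unrelated to expulsion.** The difference stays at 10.0 points. The exact false-claim rate is 5.8% to 6.0% for losses of 4%, 10% and 20%, close to the 5.6% without loss. Power at 8% v 4% falls from 80.2% with no loss to 79.8% at 4% loss and 73.3% at 20%.

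**4. Case C: lost women excluded, equal total loss L, expellers r times as likely to be lost.** The observed rate in an arm with true rate p is p(1 − rq)/(1 − L), where q = L/(rp + 1 − p). For L = 10% and r = 2 (assumed), FlexiT has q = 0.10/1.14 = 0.0877 and an observed rate of 0.14 × 0.8246/0.90 = 12.8%. NovaT has q = 0.10/1.04 = 0.0962 and an observed rate of 0.04 × 0.8077/0.90 = 3.6%. The difference is 9.2 points and the exact false-claim rate is 9.6%, against 5.8% without informative loss at the same 180 per arm. At L = 20% the difference is 8.3 points and the rate 17.2%. With r = 0.5 the bias reverses: at L = 10% the difference is 10.5 points and the rate 4.1%.

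Follow-up is equal between the arms in all three cases. The crude analysis keeps its error rate in B, exceeds it in A and in C with r = 2, and falls below it in C with r = 0.5.

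**The case against.** The strongest reply is that equal loss has no fixed direction of bias. A reader might infer that equal losses always shrink the difference. The documents do not support that, because they do not say how incompletely followed women are counted. The sample-size section speaks of a final sample of at least 384 out of 400, which suggests that women who leave the province are dropped. If their loss is unrelated to expulsion, case B applies and nothing shrinks. This stands, and it limits the point to cases A and C. It does not settle how women who stay in the province but return no questionnaire are counted. The allowance is framed around leaving the province, so they apparently stay in the sample.

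A reader might also take the 85% detection rate in the sample-size section as the study's ascertainment and conclude that the error rate is about 15%. The documents do not say so: the 85% supports an argument about efficacy lost through undetected expulsions. Visits, clinical records and questionnaires may also reveal expulsions that a woman did not notice. The 15% row is therefore an illustration only.

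Finally, partial follow-up is already addressed by the Kaplan-Meier analysis, close to complete follow-up is expected, and the operational definitions may lie in the full protocol. This is fair, and it lowers the severity. However, that analysis is labelled a check, the article gives no rule for disagreement with the crude result, and the validity sentence is wrong whatever the definitions say. Nor would Kaplan-Meier recover expulsions missed in women regarded as followed.

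**Conclusion.** The point holds in a limited form. Equal follow-up is not a sufficient condition for the validity of the crude difference against a 10-point margin. When incompletely followed women count as not expelled, or when expellers are more likely to be lost, equal loss raises the one-sided false non-inferiority rate.

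In the first case the increase is modest at the protocol's 4% allowance, about 2 points (5.6% to 7.4%, exact). It becomes large only at levels the documents do not state, such as 11.2% when 10% of expulsions are unseen. These figures rest on a Wald limit, 200 women per arm and true rates of 14% v 4%. The stronger conclusion, that the nominal error fails whenever losses are equal, is not supported. Given the small allowance, the planned check and the expected near-complete follow-up, this is a should-fix point, not a must-fix one.

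**What to change.** 1. Replace the validity sentence. State that the crude analysis is valid only if ascertainment of expulsion is essentially complete, or if lost women are excluded and loss is unrelated to expulsion. Add that equal under-ascertainment biases toward non-inferiority. State how women with incomplete follow-up are counted.
2. Make the analysis that accounts for partial follow-up primary, censoring at the last date of known device status. Alternatively, require both this and the crude analysis to have an upper limit below 10 points. Censoring of this kind still assumes that loss is unrelated to expulsion.
3. Add a tipping-point analysis for women whose 12-month device status is unknown. Vary their assumed expulsion rate by arm and report where the conclusion changes. It is needed because time-to-event methods do not correct expulsions missed in women deemed followed.

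The cost is revised wording, a little programming and a slightly wider confidence limit. No new data or participants are needed.
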